## Randomization and blinding:

After collection of baseline data, randomization will be done by computer-generated scheme with randomly permuted block sizes of 3 or 6 in a 2:1 fashion. Allocation will be concealed by consecutively numbered, sealed, opaque envelopes. Due to the nature of the intervention, blinding of subjects is not possible. whenever possible, healthcare providers will be blinded throughout the perioperative period. However, patients may report being in the study to their providers, which may inadvertently cause unblinding. Outcome adjudicators will be blinded.

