**Secondary outcomes:**

1. Descriptive outcomes of proportion of veterans eligible for inclusion, reasons for exclusion, and proportion of eligible veterans consenting to participate. Acceptability outcomes of satisfaction and use of intervention (any versus continuous) 8-weeks after randomization.

2. Smoking status at 8-weeks after randomization, as confirmed by exhaled CO.

3. Smoking reduction on the day of surgery and at 8-weeks after randomization (defined as 50% or less of baseline cigarettes smoked per day). Dual use of e-cigarettes and conventional cigarettes will also be assessed.

4. Bedside spirometry FEV1 (forced expiratory volume in first second), FVC (forced vital capacity), and cotinine level at 8-weeks after randomization (compared to baseline).

5. Postoperative complications or mortality within 30-days (by telephone self-report + chart review)

6. PACU length-of-stay

7. Hospital length-of-stay

8. Long-term assessment at 6 months - self-reported smoking status, including dual use of e-cigarettes.

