## Qualitative Method:

A semi-structured interview guide will be used at the 8-week post-randomization visit. Interviews will be audio-recorded and transcribed verbatim for subsequent analysis. The following key questions will be asked during the interview:

--> how important were e-ciagrettes/patch to you in helping you quit (what aspects)?

--> if attempting to quit again, what technique would you try and why?

--> how important was telephone counselling to you in helping you quit (what aspects)?

--> what was the most difficult challenge in quitting (what helped you overcome it)?

--> Do you smoke non-tobacco products (e.g. marijuana)? How does this effect your quitting smoking?

If not quit:

--> how interested are you in quitting now? (why this may or may not be a good time to quit)

--> how interested would you be in trying to quit another time? (why this time is preferred)

What benefits do you think you got/will get from quitting around the time of surgery?

What did you do when you had a craving to smoke a cigarette?

For e-cigarette group:

Did you use e-cigarettes and conventional cigarettes on the same day?

What made you want to use e-cigarettes versus conventional cigarettes? (what do you smoke now?)

How was this quit attempt different/similar to previous quit attempts?

Did you use non-study e-cigarette products?

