## Statistical analysis plan:

Descriptive statistics to assess feasibility:

-proportion ineligible for inclusion (95% CI by bionmial exact) and reasons for exclusion

-proportion of eligible veterans declining to participate (95% CI by binomial exact)

Baseline characteristics to be collected prior to randomization: age, gender, race/ethnicity, comorbidities (hypertension, coronary artery disease, chronic obstructive pulmonary disease, diabetes mellitus, other cardiac disease), scheduled surgical procedure and subspecialty, smoking habits (number of cigarettes per day, years smoking), Fagerstrom score for nicotine dependence. Operative day information to be collected in addition to outcomes listed below: surgical procedure, duration of surgery, anesthesia type (local/monitored anesthesia care/regional/general/combined)

| **Outcome** | **Data Description** | **Likely Distribution** | **Hypothesis Test** |
| --- | --- | --- | --- |
| Smoking cessation (primary outcome) | Proportion | n/a | Fisher’s exact test |
| Smoking reduction | Proportion | n/a | Fisher’s exact test |
| Smoking amount | Cigarettes/day, Continuous  Median (IQR) | Normal or skewed (plot histogram) | Normal: two-sided t-test  Skewed:Wilcoxon rank-sum |
| Unanticipated hospital admission | Proportion | n/a | Fisher’s Exact Test |
| Hospital length of stay | Days  Continuous  Median (IQR) | Skewed | Time-to-event using Cox proportional hazards model; graph Kaplan-Meier plot |
| 8-weeks after randomization: Agreement to (0-7 likert) "I was satisfied with product I was given (e-cigarette or patch) to help me quit" (and similar questions regarding how helpful they found it, and whether they would recommend e-cig/patch) | Likert 0-7, Ordinal, Median (IQR) | Skewed | Wilcoxon rank-sum |
| 8-weeks after randomization: During the 6-weeks after you entered the study, how often did you use the product you were given (e-cigarettes or patch)?  Everyday, most days, a few times a week, once a week, less than once a week, did not use at all | Proportion that used everyday Proportion that did not use at all. | n/a | Fisher’s exact test |
| Change in FEV1, FVC, salivary cotinine | Liters, Continuous (Mean, SD) | Normal | Paired t-test |
| Composite of 30-day postoperative complications and mortality | Proportion | n/a | Fisher’s Exact Test |
| Duration in PACU | Hours  Continuous  Median (IQR) | Skewed | Time-to-event using Cox proportional hazards model; graph Kaplan-Meier plot |

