# 16. Budget

**Awarded funding: $18,569 from internal UCSF Department of Anesthesia funds**

**Amount from UCSF RAP: $29,969**

**Total research budget: $48,538**

**Personnel-**Research Assistants

One full-time research assistant (healthcare professional with previous experience in patient interaction) at 40 hours per week and one part-time research assistant at 17.5 hours per week, each at a rate of $25.29/hr will be hired. Two research assistants are needed in order to ensure that the research assistant performing the randomization is different than the one collecting post-randomization data (i.e. to maintain blinding). We anticipate that during the first and last months of the study, we will require fewer hours since few patients will be booked for surgery within the first few weeks and no new patients will be recruited in the final 1-2 months of the study, while outcome data will continue to be collected.

Therefore, the two assistants will overlap by 4.5 months, so there will be 6 months of total coverage.

|  | Hours per week | Hourly rate | Benefits | Weekly rate | Number of weeks | Total cost |
| --- | --- | --- | --- | --- | --- | --- |
| Full-time | 40 | 25.29 | 41.72% | 1433.64 | **20** | $30,106.43 |
|  |  |  |  |  |  | $30,106.43 |

Fringe benefits are calculated using the UCSF established rates of 41.72% for 'Staff Personnel – career'.

Apart from the research assistants, no other salary support is being requested. I ([name]) have 70% protected research time, as part of the Clinical Instructorship with Research Training, that I will devote in part to this trial.

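### Outcome assessment is called blinded, but the week-8 product questions reveal the arm to the person collecting self-reported smoking and spirometry

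*Protocol*

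**What the plan says.** The Protocol, Randomization and blinding, concedes that "Due to the nature of the intervention, blinding of subjects is not possible" and then states that "Outcome adjudicators will be blinded". It does not say who the adjudicators are or which outcomes they cover.

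The one mechanism offered is in section 16 (Budget, Personnel). Two assistants are to be hired to "ensure that the research assistant performing the randomization is different than the one collecting post-randomization data (i.e. to maintain blinding"). The same section says that "the two assistants will overlap by 4.5 months, so there will be 6 months of total coverage".

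Three other places bear on what the post-randomization collector does:

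- The table in the Statistical analysis plan section lists a week-8 agreement item, "I was satisfied with product I was given (e-cigarette or patch) to help me quit", and a week-8 item on how often the assigned product was used.
- The Qualitative Method section places a semi-structured interview at the week-8 visit. Its questions refer to e-cigarettes or the patch, and one block is for the e-cigarette group only, including "Did you use e-cigarettes and conventional cigarettes on the same day".
- Secondary outcomes puts CO-confirmed smoking status, 50% smoking reduction, FEV1, FVC and cotinine at the same week-8 time point. It also lists "Postoperative complications or mortality within 30-days (by telephone self-report + chart review").

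**The concern.** Splitting randomization from data collection keeps a collector blind only if nothing in the later data reveals the arm. Here the week-8 data do so by design. Nobody can ask about satisfaction with the e-cigarette or patch, or decide whether to use the e-cigarette block, without learning the allocation.

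Participants know their arm, so a blinded assessor is one of the few safeguards left for outcomes that depend on how a question is put or how hard a participant is coached. If those outcomes are later reported as blind-assessed, the report will claim a property that the procedures do not deliver. The pilot's estimates are also meant to inform a full-scale trial, so a tilt in them would carry into its planning.

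**Working it through.** The plan gives no figure on this point, so the main check sets its sections side by side. The one power calculation concerns the satisfaction score and plays no part here.

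**Step 1. Which outcomes are exposed, and when**

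| Outcome | Time point | Sensitive to the assessor knowing the arm? | Arm revealed by the product or interview items? |
|---|---|---|---|
| Primary: smoking status, self-report plus CO below 10 ppm | Day of surgery | Self-report part yes; CO little | No, those items come later, at week 8. A dual-use question is possible, but its time point is not stated |
| Smoking status, CO-confirmed | Week 8 | Self-report part yes; CO little | Yes, unless recorded first |
| Cigarettes per day, 50% reduction | Day of surgery and week 8 | Yes; self-reported count | At week 8 yes, unless recorded first |
| FEV1, FVC | Week 8 against baseline | Yes; effort-dependent | Yes, unless recorded first |
| Cotinine | Week 8 against baseline | Little; laboratory assay | Immaterial |
| Complications or death | 30 days | Classification yes; death little | Not by these items; possibly by the chart |
| Smoking status, self-report only | 6 months | Yes | Only if the week-8 collector also does this; not stated |

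CO does not cover everything. The Budget (Equipment & Supplies) says a reading below 10 ppm confirms abstinence for the previous 24 hours, while the primary outcome uses a 48-hour window. If week 8 uses the same window, 48 − 24 = 24 hours of it rest on the answer to a question.

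**Step 2. Does the staffing rescue the claim?**

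Overlap is 4.5 of 6 months, so 6 − 4.5 = 1.5 months have one assistant. Even during full overlap the split does not help at week 8, because the collector learns the arm from the questions and not from having randomized.

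**Step 3. What a given amount of tilt would do (illustration only)**

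The document gives no misclassification rate. Assume no true effect, a true quit rate *p* in both arms, and a share *m* of e-cigarette-arm smokers recorded as abstinent.

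- Recorded e-cigarette rate = *p* + (1 − *p*)*m*, so the spurious difference = (1 − *p*)*m*.
- *p* from 4% to 65%: the control-group range in Sample size estimation. *m* from 5% to 20%: my assumption.
- Smallest: (1 − 0.65) × 0.05 = 0.0175, or 1.75 points. Largest: (1 − 0.04) × 0.20 = 0.192, or 19.2 points.
- Rejection rate of Fisher's exact test, 20 against 10, two-sided 5%, at *p* = 4%, 20%, 40% and 65%: 0.3% to 3.3% with *m* = 0, and 0.1% to 8.7% with *m* between 5% and 20%.

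In this illustration the test seldom rejects. The effect falls mainly on the point estimate, which is what the pilot is meant to supply. For CO-confirmed abstinence the upper values are unlikely, since only smokers reading below 10 ppm could be miscounted. The reduction outcome rests on a self-reported count and has no such limit.

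**The case against.** The strongest reply is that the sentence about adjudicators may refer to people other than the data collector, such as someone classifying complications from charts. No section says outright that one person runs the CO test, the spirometry and the interview. This stands in part: the sentence is undefined, and not shown to be false for every outcome. But the Budget itself ties blinding to the assistant who collects post-randomization data, and names no other assessor.

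A second reply is that the order of items within a visit belongs in the case report form or a manual. Its absence alone would not be a finding. The difficulty is that the protocol asserts blinding and gives a mechanism that its own week-8 content defeats.

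Four stronger readings are tempting and are not supported:

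- **The primary outcome is unblinded.** The satisfaction, use and interview items come at week 8, after that participant's day-of-surgery assessment. Disclosure on the day is possible, because participants know their arm and a dual-use question may be asked, but the document does not force it.
- **CO and cotinine are compromised.** One is an instrument reading against a fixed cut-off and the other a laboratory assay.
- **Every control's chart reveals the arm.** Controls get a patch prescription supplied through the VA pharmacy, so the chart may show it. No section says what the person classifying complications sees.
- **The 1.5 single-assistant months break the split.** They may fall at the start, with only randomization to do, or at the end, with only collection.

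Nor is it evidence of bias that one reclassified control moves that arm by 10 points. That is simply 1/10.

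**Conclusion.** The concern holds for the week-8 assessments. As the Budget describes the role, the post-randomization collector cannot stay blinded through that visit, and nothing places self-reported smoking status, cigarettes per day, FEV1 and FVC before the disclosure. Up to all 30 planned week-8 visits are affected, assuming full follow-up, one collector per visit and product items asked first. The document neither requires nor prevents that order.

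The size of any bias cannot be derived from the document; the range of 1.75 to 19.2 points rests on an assumed misclassification share. The primary outcome is at most exposed to an unaddressed risk of disclosure, and chart review for complications is a reasonable inference of the same kind. This is a correction worth making before enrolment, and not a challenge to the validity of the primary comparison.

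**What to change.** 1. **Week 8.** Ask scripted questions on smoking status and cigarettes per day, then take CO, spirometry and saliva. Lock these entries before any product-use, dual-use, satisfaction or interview item.
2. **Day of surgery.** Record smoking status and CO before any dual-use question, and add no other product question. The week-8 sequence should not be carried over to this day: it would bring in unscheduled items and reveal the arm before the 30-day and week-8 assessments.
3. **Complications.** Where feasible, classify 30-day events from chart extracts with medication lists and mentions of smoking aids removed.
4. **Wording.** In Randomization and blinding, list which outcomes are assessed blind and by whom, and describe the rest as open-label.

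The cost is a reordered form and modest work to prepare up to 30 chart extracts, which someone other than the classifier should do. Sample size, treatment and visit schedule are unchanged. Participants may still volunteer their arm early, so the order reduces the exposure without removing it.

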## Techniques to maximize adherence:

To maximize follow-up, patients will be provided with an incentive of $40 to participate in the study to its completion. To ensure research staff adhere to the protocol, the principal investigator (PI) or co-investigator (CI) will personally observe the recruitment, consent, randomization, and intervention for the first 3 patients enrolled. The duration, frequency, and timing of all in-person sessions and level of subject’s engagement (number and type of questions) during the session will be recorded by the research staff.

## Safety of NJOY e-cigarettes:

E-cigarettes in the USA are not FDA-regulated as drugs or medical devices and there is limited safety data regarding e-cigarettes. However, a recent systematic review of worldwide e-cigarettes determined that e-cigarettes are a less harmful alternative to smoking and significant health benefits are expected in smokers who switch from tobacco to electronic cigarettes[^38^](#_ENREF_38). Specifically, there were no serious adverse events reported in the two randomized controlled trials that have included detailed e-cigarette safety analyses. There are published data on NJOY e-cigarettes[^39^](#_ENREF_39), including a study that showed that NJOY King Bold disposable e-cigarettes (same type proposed for use in this study) when used in the short-term did not have any serious adverse events in a sample of 29 regular smokers that did not intend to quit. All but one of the 15 adverse events were mild and local, with most resolving within the first few days of use as subjects became more familiar with the product. The most common adverse events were mouth, throat, or airway irritation (7), followed by cough (2) and dry throat (1). One subject experienced intermittent headaches and one subject experienced a burning sensation on lips. The only "moderate" adverse effect was throat irritation that required discontinuing use of the product. Other findings in the study included reduced exhaled carbon monoxide levels, cravings for cigarettes and withdrawal symptoms. Mild heart-rate elevation of up to 5 beats per minute in the first 10 minutes of use was noted. After one-week of use, mean cigarette use was reduced in 89% of subjects.

NJOY e-cigarettes are easily and widely available, both online and in shops that sell cigarette products, from small local stores to large chains like Costco or Wal-mart. Despite the fact that there are no e-cigarettes in the United States that are FDA approved for smoking cessation, a content analysis of e-cigarette retail website marketing found that 95% of websites made explicit or implicit health-related claims, 64% had a smoking cessation-related claim and 22% featured doctors[^40^](#_ENREF_40). Preoperative patients believe that e-cigarettes can help them quit smoking, as shown in a survey of 112 elective surgery patients, where 71% of respondents cited smoking cessation as a the reason they had tried e-cigarettes and 62% of respondents felt switching to e-cigarettes would improve their health around the time of surgery[^25^](#_ENREF_25).

## Adverse events, side effects, and interim monitoring:

Subjects will be asked both open-ended and checklist-based questions to monitor for safety.

Safety data regarding e-cigarette use is limited, but the following have been reported and will be monitored:

-headache, nausea, oropharynx irritation, dry cough (persistent or intermittent)

-pneumonia (requiring antibiotics, requiring hospitalization)

Patients will be able to contact a member of the research team by pager at any time to report adverse events and seek assistance. We do not plan unmasked interim monitoring. However, if any catastrophic adverse event is suspected to be related to the study (deemed to be life-threatening), we will unblind that subject for safety and the study will be stopped early if the life-threatening adverse event is thought to be directly related to the study intervention. [name], SFVAMC anesthesiologist with extensive experience in clinical research and research ethics, has agreed to serve as an independent data safety monitoring officer for the study.

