We plan to carry-out a pilot randomized controlled trial with parallel design comparing e-cigarettes and telephone counselling with transdermal nicotine replacement and telephone counselling. Our primary outcome is smoking cessation on the day of surgery, as confirmed biochemically by exhaled carbon monoxide. Smoking reduction (self-reported cigarettes per day) of 50% or more and bedside spirometry readings will be assessed as secondary outcomes.

**» Aim 2) To determine the acceptability of e-cigarettes amongst veterans as an aid for smoking cessation and to determine the feasibility of recruitment, randomization, and follow-up procedures in preparation for large-scale trial.**

Through implementation of this pilot trial, we will determine the feasibility and acceptability of e-cigarettes for smoking cessation perioperatively in the veteran population and obtain the preliminary data necessary to run a larger trial on the effectiveness of e-cigarettes as a perioperative smoking cessation aid.

**» Aim 3) To determine the safety of e-cigarettes as a harm reduction strategy to achieve short-term perioperative smoking cessation.**

We plan to improve the overall knowledge of the safety of short-term e-cigarettes use through careful surveillance for adverse events and side effects.

**» Aim 4) To determine if e-cigarette use preoperatively is associated with a lower risk of complications postoperatively.**

We plan to measure the following secondary outcomes: postoperative complications and mortality within the first 30 days, post-anesthesia care unit (PACU) length-of-stay, and hospital length-of-stay. This will help us understand if e-cigarettes have the potential to be used for harm-reduction perioperatively.

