**Exclusion criteria:**

Emergency surgery (booked <24 hours preoperatively)

Consumers of non-cigarette forms of tobacco only (pipe, smokeless tobacco) or marijuana only

Already enrolled in a smoking cessation trial or current smoking cessation pharmacotherapy

Already daily users of e-cigarettes or previous adverse reaction to e-cigarette or transdermal nicotine

Poor proficiency of English language**¸**as indicated by need for an interpreter (including family members) at the preadmission visit

Lacking capacity for consent (e.g. due to mental illness or dementia)**,** as indicated by consent for surgery and other medical procedures being obtained from a substitute decision maker

Pregnant or breastfeeding

Unstable cardiac condition (unstable angina, unstable arrhythmia)

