## Ethical considerations:

Ethics approval from the UCSF committee on human research institutional review board and SFVAMC will be obtained prior to commencement of the study. Written, informed consent, will be obtained by all patients prior to trial enrollment. E-cigarettes are a widely available commercial product that are often marketed and used as a means for current smokers to quit smoking[^41^](#_ENREF_41). Recently, the FDA has issued a proposed rule that would extend the agency’s tobacco authority to cover additional products that meet the legal definition of a tobacco product, such as e-cigarettes; however, currently, e-cigarettes are not an FDA-approved form of nicotine replacement therapy (<http://www.fda.gov/newsevents/publichealthfocus/ucm172906.htm>; accessed 9/22/2014). The use of e-cigarettes may be associated with harms greater than those of NRT. These risks will be told verbally and in written format to potential study participants. The largest randomized trial to date (657 participants) investigating e-cigarettes versus nicotine patches did not find an increased adverse event rate in the e-cigarette group, indicating that short-term use of e-cigarettes is likely safe, although the adverse event rate may differ in the veteran population[^10^](#_ENREF_10). Furthermore, there is variability in the quality of commercially available products and the most-studied brand of e-cigarette is not widely available in the USA. We have therefore chosen to study a brand that has at least some published experimental and safety data.

Currently, smokers presenting for surgery receive brief pre-operative advice, but no other intervention regarding smoking cessation. Thus, even if e-cigarettes are not more beneficial than NRT, both arms of the study are receiving care that is likely better than the current standard, due to the incorporation of counselling in both the control and intervention groups.

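### The events named for safety monitoring all come from e-cigarette reports and none is specific to the nicotine patch, so by-arm adverse-event counts are at risk of uneven ascertainment

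*Protocol*

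**What the plan says.** The protocol's section on adverse events, side effects and interim monitoring sets out how safety data are obtained. "Subjects will be asked both open-ended and checklist-based questions to monitor for safety". It then gives the events to be watched for, introduced by "Safety data regarding e-cigarette use is limited, but the following have been reported and will be monitored". Five are named: headache, nausea, oropharynx irritation, dry cough and pneumonia. A third route is open to everyone: "Patients will be able to contact a member of the research team by pager at any time to report adverse events and seek assistance".

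Aim 3, under Specific Aims, concerns the safety of e-cigarettes and promises "careful surveillance for adverse events and side effects". The control arm is prescribed six weeks of transdermal nicotine (Control and intervention groups), and the exclusion criteria include "previous adverse reaction to e-cigarette or transdermal nicotine". Ethical considerations says: "The use of e-cigarettes may be associated with harms greater than those of NRT". The outcome table in the Statistical analysis plan section has no adverse-event row.

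**The concern.** A named prompt and an open question are not equivalent ways of eliciting an event. Reactions typical of the e-cigarette have three routes into the data: the open question, the checklist item and the pager. A reaction typical of the patch has two, because no item names it. If events are then counted by arm, part of any excess in the e-cigarette arm could come from how the question was put.

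At stake is what the pilot hands on. The section on future funding says that the full-scale trial will lean towards Aims 2 to 4 and will again compare e-cigarettes with nicotine replacement head to head. Safety is Aim 3, so both the event counts and the collection method are likely to be carried forward. An event that was never elicited cannot be recovered at analysis.

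**Working it through.** The protocol gives no adverse-event rate, capture rate or safety power figure, so there is nothing of its own to reproduce on this point. Its one power figure concerns satisfaction: (1.960 + 0.842) × √(1/10 + 1/20) = 1.085, which matches the text but does not bear on safety.

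**Reading the text**

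1. *Source of the list.* The introductory sentence ties it to e-cigarette safety data. The content agrees with the small study summarised under Safety of NJOY e-cigarettes. Of its 15 adverse events, 7 were mouth, throat or airway irritation, 2 were cough and 1 was dry throat, and one subject had headaches.
2. *Patch items.* None of the five is particular to a product worn on the skin.
3. *Who is asked.* The checklist sentence refers to subjects without distinguishing arms. The Budget section also wants post-randomization data collected by a different assistant from the one who randomizes, to maintain blinding, which fits a common form better than arm-specific ones. The listed items are therefore probably prompted equally in both arms.
4. *What remains uneven.* Only reactions that are not listed, and any total that includes them.
5. *Blinding.* Subjects know their product. Blinded adjudicators can classify only what has been reported.

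**Illustration of size (assumed inputs)**

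Let p be the true proportion with an event, equal in both arms. Let s be the share of unlisted patch reactions that open questioning catches, relative to full capture in the e-cigarette arm. Let f be the share of affected patch users who have at least one listed event and so are caught anyway. None of these is in the documents. The arm sizes, 20 and 10, are from Sample size estimation.

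Observed patch proportion = p × [f + (1 − f)s]. Apparent risk ratio (e-cigarette/patch) = 1 / [f + (1 − f)s].

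- f = 0 (product-specific reactions only): s = 0.75, 0.50, 0.25 gives ratios of 1.33, 2.0 and 4.0.
- f = 0.5: ratios of 1/0.875 = 1.14, 1/0.75 = 1.33 and 1/0.625 = 1.60.
- f = 1: ratio 1, no distortion.

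For f = 0, the spurious difference is p(1 − s). The approximate 95% half-width is 1.96 × √[p(1 − p)/20 + ps(1 − ps)/10]. The last column is the exact probability that a two-sided Fisher test on 20 versus 10 rejects at 0.05.

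| p | s | Spurious difference (points) | Half-width (points) | Fisher rejection |
| --- | --- | --- | --- | --- |
| 0.30 | 1 | 0 | – | 3.1% |
| 0.30 | 0.75 | 7.5 | 32.8 | 3.4% |
| 0.30 | 0.50 | 15 | 29.9 | 6.3% |
| 0.30 | 0.25 | 22.5 | 25.9 | 12.2% |
| 0.50 | 1 | 0 | – | 2.6% |
| 0.50 | 0.75 | 12.5 | 37.2 | 5.7% |
| 0.50 | 0.50 | 25 | 34.6 | 18.2% |
| 0.50 | 0.25 | 37.5 | 30.0 | 46.6% |

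The direction is the same throughout, against e-cigarettes. The distortion is smaller than sampling error in every row except the last. With 10 controls, one patch user whose only reaction goes unrecorded moves the control proportion by 10 points.

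**The case against.** The case for leaving the section alone has real weight.

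- *Emphasis on the less-known product is reasonable.* E-cigarettes lack FDA approval and have limited safety data, while the patch is on the VA formulary. This stands as a reason to name e-cigarette events. It is not a reason to omit patch events when the patch is the only comparator.
- *Patch users are asked.* A reader might infer that patch reactions depend on spontaneous mention. They do not: open-ended questions are put to all subjects, and the pager is available to all. This stands. What is missing is the named prompt.
- *Listed events are asked alike.* A reader might infer that every event-by-event comparison is tilted. The text makes no arm distinction, so comparisons of headache, nausea, throat irritation, cough and pneumonia are not affected.
- *The checklist may be longer than the list.* The protocol does not say that it is limited to these five events. That is true, but nothing in the protocol secures a patch item either.
- *No safety comparison is planned.* A reader might infer that a specified analysis is biased. Aim 3 states no contrast, the outcome table has no adverse-event row, and the remark in Ethical considerations about harms relative to NRT concerns risk disclosure. This stands as to formal testing. Even so, adverse events from a randomized trial against NRT will naturally be set out by arm.
- *The size is assumed.* This also stands. The larger ratios require that no affected patch user has a listed event, which is doubtful when both products deliver nicotine.

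**Conclusion.** The point holds in a limited form. The protocol fixes a monitored list drawn from one product's reported events and names nothing specific to the other. Any by-arm count of overall or product-specific adverse events is therefore at risk of differential ascertainment that makes e-cigarettes look worse.

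This rests on two readings: that the checklist contains only the named items, and that a named prompt elicits more than an open question. The documents confirm neither outright. They give no basis for a size, and the ratios above, 1.14 to 4.0, only show how strongly the answer depends on assumed capture and overlap. They do not support saying that a planned safety comparison is biased, or that this bias would dominate with 20 against 10 subjects. At an assumed 30% event rate, sampling error is larger in every case shown.

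It is a cheap improvement worth making before data collection, and it does not threaten the primary outcome.

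**What to change.** In the section on adverse events, side effects and interim monitoring, state that:

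- one common checklist is used in both arms, and it is asked after the open-ended question so that the prompts do not shape the free answer;
- it keeps the current five items and adds the anticipated reactions to transdermal nicotine, which the investigators should list;
- solicited events (from the checklist) and unsolicited events (from the open question or pager) are tabulated separately by arm, with exact 95% confidence intervals.

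The intervals will be wide and should be shown as such. With no events, the upper limit is 1 − 0.025^(1/20) = 16.8% for 20 subjects and 1 − 0.025^(1/10) = 30.8% for 10.

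The cost is a few more checklist lines and one table. The downside is that more minor events will be recorded, mainly in the control arm. Treatment and sample size do not change.
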